In agreement with the previous studies, we also demonstrated the beneficial effects of high molecular weight β-glucan in healthy adults in a recent randomized, controlled-diet, crossover trial (n = 35). The results showed that consumption of 3 g or 5 g per day of high molecular weight barley β-glucan is highly effective in reducing TC and LDL cholesterol in adults with moderate hypercholesterolemia [32].

Long-chain PUFAs such as eicosapentaenoic acid (EPA) and DHA from fish and marine source oils, including algal oil, have commercially emerged as dietary supplements due to their health benefits. Long-chain fatty acids, including DHA, were shown to lower TG and increase serum HDL-C concentrations [33]. DHA is also capable of acting as an antiatherogenic factor by inhibiting inflammatory processes and thereby inhibiting plaque formation [34]. On the basis of the vast amount of knowledge accumulated over the years, the American Heart Association has recommended the use of n-3 fatty acids, including DHA, for secondary prevention of cardiovascular events in people with documented coronary artery disease.

Considering the fact that CVD is a multifactorial disease, the dietary approaches that combine different bioactives with enhanced health benefits have recently been well elucidated. For instance, a portfolio containing a low-fat vegetarian diet enriched by the inclusion of PSs, soy protein, viscous fiber, and tree nuts has been shown through our collaborations to markedly reduce LDL-C concentrations to an extent comparable in magnitude with reductions achieved using first-generation statins [35, 36]. Likewise, a large body of research has demonstrated the synergetic effects attained by introducing two or more food bioactive components into the diet to achieve maximal health benefits through multimechanistic effects [37–39]. Accordingly, combining highly bioactive components such as HOCO, barley β-glucan, and DHA is expected to produce great synergistic and pleotropic beneficial effects on CVD risks factors compared with the individual biological actions listed above.

The overall objective of the present study is to test novel foods containing the most effective bioactives, including n-3 fatty acid–enriched dietary oil high in MUFAs and soluble dietary fiber, with aims of managing CVD risk factors in people with MetS and testing the efficacy and safety of these dietary components in humans.

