The four treatments are as follows: (1) muffins and cookies containing all-purpose flour and 50 g/day HOCO-DHA (85 %/15 %; DHA oil consists of 40 % DHA) (DHA dosage 3 g/day); (2) muffins and cookies containing barley flour with 4.36 g/day of high molecular weight barley β-glucan and 50 g/day of a blend of sunflower oil, safflower oil, and butter as a control oil; (3) muffins and cookies containing a combination of barley flour with 4.36 g/day, high molecular weight barley β-glucan, and 50 g/day of HOCO-DHA; and (4) muffins and cookies containing all-purpose flour and 50 g/day of control oil. The control oil used in the study represents a typical Western diet fat intake as a control treatment composed largely of saturated fat with substantial levels of n-6 linoleic acid common in current North American dietary intakes. Dosages for HOCO-DHA and barley β-glucan were determined on the basis of previous clinical studies done by our research group [20, 21, 32]. Muffin and cookie recipes were developed in Agriculture and Agri-Food Canada laboratories at the RCFFN metabolic kitchen. Barley grain (cultivar CDC Rattan) was provided by the Alberta Barley Commission and milled into whole grain flour by the Canadian International Grains Institute. All-purpose flour was obtained from local supermarket. HOCO was provided by Richardson Oilseed Limited. life’s DHA oil was purchased from DSM Nutritional Products (Ayr, ON, Canada). Macronutrients, including protein, carbohydrates, and fiber content of the foods, were analyzed at the Agriculture and Agri-Food Canada laboratories, RCFFN, Winnipeg, Canada. Total fat and fatty acid profiles of the foods were measured at the RCFFN laboratories (Winnipeg, MB, Canada). The muffin flavors include vanilla and spice, and the cookies were made in lemon, ginger, and chocolate flavors. The flavors of the muffins and cookies will be provided in rotation with equal numbers of days per flavor during each treatment period. The nutrient compositions of the muffins and cookies for the different treatments of the study are depicted in Tables 1 and 2, respectively. The macronutrient contents of treatment foods will be similar between different treatments, and also there are no differences in nutritional values between different flavors of muffins or cookies.

**Table 1 Tab1:** Details and nutritional composition of the study muffins

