### Sample size calculation and statistical analysis

Sample size was determined to detect an anticipated difference in LDL-C level of 7.4 % (0.43 mmol/L) due to HOCO consumption, compared with control, with a standard deviation estimate of 0.13 mmol/L. The α and power were taken as 0.05 and 0.8, respectively. A sample size of 35 participants was therefore calculated, with a target of 28 participants, taking into account the block size and the estimated 20 % premature withdrawal rate of participants from the protocol, given the existing level of difficulty in completing the protocol elements.

Statistical analysis will be performed using SAS statistical software (SAS Institute, Cary, NC, USA). Baseline and endpoint measurements will be compared using the analysis of variance (ANOVA) model for determination of treatment effects. The results will be expressed as means with standard errors. The normality of distribution of data will be determined with the Shapiro–Wilk test, and the non-normal variables will be normalized before comparison with other treatment by log transformation. The effects of dietary treatments will be examined using mixed-model ANOVA with diet, sequence, phase, and center as fixed factors and subject as a random factor within the model. Statistical significance will be set at *p* < 0.05 for all analyses. Significance between different dietary effects will be examined with the Bonferroni adjustment for multiple comparisons.

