## Discussion

Considering the huge health impact of dietary portfolio intervention approaches as highly efficient nutritional strategies for the modification of CVD risk factors, combination of food components and bioactives are getting tremendous attention as an alternative strategy to manage CVD risk factors. We anticipate that, taken together, the foods containing both HOCO-DHA and barley-derived high molecular weight β-glucan will possess a superior biological action due to their differential mechanistic effects, compared with the individual components, against CVD risk factors.

In the current proposal, combining these potent groups of food bioactives, such as HOCO-DHA and β-glucan, to achieve parallel multiplication of biological action and to reduce the CVD events substantially is of paramount clinical significance. This study will be the first investigation of the cholesterol-lowering effect of a combination of HOCO-DHA and barley β-glucan. The proposed study will help to improve understanding of the metabolic mechanisms underpinning the health benefits associated with consumption of foods consisting of HOCO-DHA and barley β-glucan. The proposed research will not only support the improvement of the cardiovascular health of Canadians but also increase the marketability of our canola-barley products internationally. The anticipated outcomes of the proposed study are expected to have a high probability of impacting the health and wellness of Canadians because (1) a significant proportion of the population has MetS and (2) scientific data generated by well-designed, unbiased human clinical trials are required to properly substantiate health effects of a combination of HOCO-DHA and barley β-glucan.

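### The protocol expects synergy from a 2x2 set of diets but names no oil-by-flour contrast, and comparisons between pairs of diets cannot separate synergy from additive effects

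*Protocol article*

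**What the plan says.** The Methods/Design section of the protocol article describes four treatments: HOCO-DHA oil with all-purpose flour, control oil with barley flour, HOCO-DHA oil with barley flour, and finally "muffins and cookies containing all-purpose flour and 50 g/day of control oil". Every participant is to receive all four, in a Latin square order.

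The Background says that combining the components "is expected to produce great synergistic and pleotropic beneficial effects on CVD risks factors compared with the individual biological actions listed above". The Discussion expects that the combined foods "will possess a superior biological action due to their differential mechanistic effects, compared with the individual components", and goes on to describe the aim of combining them in terms of multiplied action.

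Under Sample size calculation and statistical analysis, the plan is: "The effects of dietary treatments will be examined using mixed-model ANOVA with diet, sequence, phase, and center as fixed factors", with subject as a random factor. Differences between diets are then examined with a Bonferroni adjustment. Variables that fail a Shapiro–Wilk test are log-transformed. The sample size rests on one contrast, an "anticipated difference in LDL-C level of 7.4 % (0.43 mmol/L) due to HOCO consumption, compared with control".

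**The concern.** In a 2x2 layout, synergy means that the two components together do more than the sum of what each does alone. That is the oil-by-flour interaction, and it involves all four diets at once. The article fixes the model factors, the significance level and the way diets are compared, but this contrast is not among them.

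If the analysis is done as written, the natural reading of a good result would be that the combination lowered LDL-C more than control and more than each component, and that the expected synergy was therefore confirmed. Two components that simply add would give the same set of significant comparisons. The trial has the data to answer the question that its Background raises, but the stated analysis does not ask it.

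**Working it through.** **The plan's own figure.** The sample size section gives these inputs: difference 0.43 mmol/L, SD 0.13 mmol/L (of what is not stated), α 0.05, power 0.80. Two-sided testing is assumed. The result it reports is: "A sample size of 35 participants was therefore calculated, with a target of 28 participants".

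- Reading 0.13 as the SD of within-person differences: n = (0.13 × (1.96 + 0.84) / 0.43)² = 0.72, which rounds up to 1. An exact paired t calculation gives 3.
- Reading 0.13 as the within-person SD per phase: n = 2 × 0.72 = 1.43, which rounds up to 2. The exact t calculation gives 4, or 6 with Bonferroni over six comparisons.
- Only the withdrawal step reproduces: 28 / (1 − 0.20) = 35.
- 0.43 mmol/L as 7.4% implies a reference LDL-C of 0.43 / 0.074 = 5.81 mmol/L.

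The stated 28 and 35 therefore do not follow from the stated inputs.

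**What each comparison estimates.** Write C, O, B and OB for mean LDL-C on control, HOCO-DHA only, barley only and the combination. The synergy contrast is OB − O − B + C; a negative value means extra lowering. Four diets give 4 × 3 / 2 = 6 pairwise differences. Each uses two diets, so none equals the contrast.

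Under pure additivity, with an oil effect of 0.43 (the planning value) and a barley effect b:

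- OB − C = −(0.43 + b)
- OB − O = −b
- OB − B = −0.43
- OB − O − B + C = 0

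The documents give no b, so it is an assumption here. The table shows the power of the combination versus HOCO-DHA-only comparison at 28 completers (two-sided 0.05/6, noncentral t with 78 df) when synergy is exactly zero:

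| Assumed b (mmol/L) | 0.13 = within-person SD | 0.13 = SD of differences |
|---|---|---|
| 0.10 | 57% | 91% |
| 0.12 | 77% | 98% |
| 0.215 | over 99.9% | over 99.9% |

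Combination versus barley only, at 0.43, exceeds 99.9% under either reading. Both combination-versus-component comparisons can thus be significant with no synergy at all.

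**Is the model adequate?** With 28 completers and four phases, residual df = 112 − 1 − 27 (subjects) − 3 (phases) − 3 (diets) = 78. On one simulated 28 × 4 Latin-square data set, the four-level diet model and the oil + flour + oil × flour model had the same residual sum of squares and the same 78 df. The contrast from the first equalled the interaction coefficient from the second (−0.0520). They are one model in two parameterisations.

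**Precision.** With within-person SD s and n completers:

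- Pairwise difference: SE = s√(2/n)
- Main effect pooled over the other factor: SE = s/√n, which is 1/√2 of the pairwise SE
- Interaction: SE = 2s/√n, which is √2 times the pairwise SE

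With s = 0.13 and n = 28 these are 0.0347, 0.0246 and 0.0491 mmol/L. The interaction detectable with 80% power is 2.80 × 0.0491 = 0.138. If 0.13 is instead the SD of differences, it is 0.138 / √2 = 0.097.

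**Scale.** If each component multiplies LDL-C, by factors a and c, the contrast is zero on the log scale but C(1 − a)(1 − c) on the raw scale. Assuming a 7.4% reduction for each and C = 5.81, that is 5.81 × 0.074² = 0.032 mmol/L. This is small for LDL-C, but it shows that the meaning of no synergy changes if the data trigger the log transformation.

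**The case against.** The strongest reply has three parts.

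- **Synergy is not the formal objective.** The Abstract and the closing paragraph of the Background speak of effects on CVD risk factors, efficacy and safety. This stands: synergy is an expectation. The Discussion's milder expectation, that the combination outperforms each component, can be tested by the planned comparisons between diets.
- **The model blocks nothing.** A reader might infer that a single diet factor makes a synergy test impossible and has to be replaced. The equivalence shown above rules that out.
- **An analysis plan that is not shown may name the contrast, and the article does not list its comparisons as exactly six pairs.** This is possible. But the article does fix the factors and the comparison method, and what it fixes does not match its own rationale. Adding the contrast costs almost nothing.

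A reader might also infer that comparing diets in pairs wastes power, or that synergy below about 0.6 mmol/L could never be shown. The documents support neither. On the stated 0.43 and 0.13, every pairwise test sized at 0.43 has over 99.9% power, even with Bonferroni over six. The 0.6 figure comes from assuming that 28 completers give exactly 80% pairwise power at 0.43. That requires an SD of differences of 0.43 × √28 / 2.80 = 0.81, about six times the stated value, and it makes the detectable interaction √2 × 0.43 = 0.61. Pooled main effects are more precise, but they describe each component's own effect only if there is no interaction, which is the very thing in question.

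**Conclusion.** The point holds in a limited form. The diets are a complete 2x2, synergy is expected, and no stated comparison can tell synergy from additivity. The defect is one unnamed contrast; the model and the data are sufficient. It does not invalidate the planned diet comparisons. It matters for what may be concluded about the combination.

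The SE ratios (1/√2 and √2) assume equal within-person variance and complete data, and do not depend on the SD. The detectable interaction of about 0.10 to 0.14 mmol/L holds only if 0.13 is right, with the range reflecting its two readings. Because 0.43, 0.13 and 28 cannot all be inputs and output of one calculation, neither this range nor any other detectable synergy should be stated in the plan until they are reconciled.

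**What to change.** Keep the mixed model. Add the following before the data are analysed:

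- For LDL-C, pre-specify the contrast combination − HOCO-DHA only − barley only + control, reported with its estimate and 95% CI.
- State the scale (raw or log) on which it is assessed, so that the normality test does not decide what synergy means.
- State whether it lies inside or outside the Bonferroni family.
- Make it the only basis for a statement of synergy.
- For a statement that the combination is better than its components, require both the comparison with HOCO-DHA only and the comparison with barley only.
- Optionally, report pooled main effects beside the simple effects.
- Reconcile the difference, SD and sample size before giving any power for the interaction.

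The cost is a contrast statement and a few sentences, with no new data. If the contrast joins the Bonferroni family, the other comparisons face a slightly stricter threshold (0.05/7 instead of 0.05/6, if all pairs are compared). Its CI will also be √2 times as wide as that of a pairwise difference at the same confidence level, so an inconclusive result on synergy has to be reported as such.

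### Bonferroni for the diet comparisons is valid, but a step-down test gains up to about 12 points of power per contrast at the same 5% familywise error, depending on assumptions

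*Protocol article*

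**What the plan says.** All of the relevant text but one sentence is in the section 'Sample size calculation and statistical analysis'.

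- Multiplicity: "Significance between different dietary effects will be examined with the Bonferroni adjustment for multiple comparisons". No step-down variant is named, so single-step Bonferroni is the natural reading. The number of comparisons in the family is not given.
- Level: "Statistical significance will be set at *p* < 0.05 for all analyses".
- Planning: "The α and power were taken as 0.05 and 0.8, respectively", for an "anticipated difference in LDL-C level of 7.4 % (0.43 mmol/L) due to HOCO consumption, compared with control", "with a standard deviation estimate of 0.13 mmol/L". No multiplicity allowance is mentioned here.
- Size: "A sample size of 35 participants was therefore calculated, with a target of 28 participants", the gap being the "estimated 20 % premature withdrawal rate of participants from the protocol".

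The Discussion expects that foods with both ingredients "will possess a superior biological action due to their differential mechanistic effects, compared with the individual components". That expectation concerns combination versus oil alone and combination versus barley alone. It is not declared as a formal test.

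**The concern.** Four diets give 4 × 3 / 2 = 6 pairs. Single-step Bonferroni then tests every pair at 0.05/6 = 0.0083, whatever the other comparisons show. That is stricter than 5% familywise control requires. Once one equality among four means is rejected, at most three of the other five can be true together: if any two diets differ, the most equalities possible is three diets alike and one apart. A step-down test uses such facts to relax the later thresholds.

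At stake is power for the smaller contrasts. If both ingredients work, combination versus control is the largest contrast and is rejected first. The single-component contrasts, and those between the combination and its components, come afterwards, where a step-down rule is more lenient.

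**Working it through.** **1. The plan's own figures.** The withdrawal step reproduces: 28 / (1 − 0.20) = 35. The 28 does not. With n = ((1.960 + 0.842) × SD / difference)², n = (2.802 × 0.13 / 0.43)² = 0.7 if 0.13 is the SD of a within-person difference. It is 1.4 if 0.13 is a within-person SD (variance doubled). With the t distribution 3 or 4 participants are needed. For 28 to give 80% power, the SD of the difference would have to be about 0.43 × √28 / 2.802 = 0.81 mmol/L.

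**2. Two calibrations.**

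- *Literal inputs.* Noncentrality = 0.43 × √28 / 0.13 = 17.5, or 0.43 × √14 / 0.13 = 12.4 under the two readings of the SD. Power is about 100% with Bonferroni, Holm and Shaffer alike, so the gain is 0.
- *Nominal power (assumption).* Take at face value that one contrast has 80% power at two-sided 0.05 with 28 completers. Residual degrees of freedom: 112 observations − 1 − 27 (participants) − 3 (phases) − 3 (diets) = 78. The required effect is 0.758 within-person SDs (noncentrality 0.758 × √14 = 2.84). At 0.05/6 that contrast has 55% power; at 0.05/3 it has 65%.

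**3. Divisors of 0.05, from the smallest p-value up (six pairs).** Bonferroni 6,6,6,6,6,6; Holm 6,5,4,3,2,1; Shaffer 6,3,3,3,2,1.

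**4. Simulated power for HOCO-DHA versus control** at the nominal calibration (100,000 trials per pattern, four diet means with a common residual variance):

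| True pattern | Bonferroni, 6 pairs | Holm, 6 pairs | Shaffer, 6 pairs | Bonferroni, 3 vs control | Holm, 3 vs control |
|---|---|---|---|---|---|
| Oil and barley equal, additive | 55% | 65% | 67% | 65% | 76% |
| Barley half as large, additive | 55% | 61% | 65% | 65% | 71% |
| Oil effect only | 55% | 60% | 63% | 65% | 68% |
| All three active diets equal | 55% | 58% | 62% | 65% | 73% |
| Only the oil diet differs | 55% | 58% | 62% | 65% | 65% |

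With six pairs Holm gains 3 to 10 points and Shaffer 7 to 12. With three comparisons against control Holm gains 0 to 11. Familywise error was at most 4.3% for every adjusted method with six pairs and at most 4.5% with three comparisons.

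**5. Combination better than both components (six pairs, both contrasts significant).**

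| True pattern | Bonferroni | Holm | Shaffer |
|---|---|---|---|
| Equal, additive | 39% | 52% | 53% |
| Barley half as large | 9% | 14% | 15% |
| Oil effect only | about 0% | about 1% | about 1% |

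In the equal additive pattern, combination versus control is rejected in 99.8% of trials, so the relaxed thresholds nearly always apply. In the oil-only pattern the combination is truly no better than oil, so there is nothing to gain.

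**6. Dependence on effect size.** With six pairs, across the patterns tried, the gain is 1–5 points at noncentrality 1.5, 2–5 at noncentrality 4, at most 1 at 5, and none from 6 upwards.

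**The case against.** Bonferroni is a legitimate prespecified choice. Nothing in the section is wrong or contradictory on this point, and single-step tests agree with their simultaneous intervals, which is a respectable reason to prefer them. This stands: the point concerns efficiency only.

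The article does not say that six pairs form the family, and the only contrast it singles out is HOCO versus control. A fuller protocol or an SAP, not among the documents reviewed, may define the family. This also stands, which is why both families are shown. Shaffer's argument does not carry over to comparisons with control only.

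At the plan's literal inputs there is nothing to gain. That is true and limits the point. Those inputs need only a handful of participants, though, so they cannot be what produced 28. The same adjustment also appears to govern the other outcomes, for which no effect or SD is given.

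A reader might infer that Bonferroni costs this trial 5 to 12 points outright, or that its real power is 55%. The documents support neither. They fix neither the family nor the effects of the other diets, and the 80% calibration is an assumption. Nor can the Discussion's expectation be read as a declared test that Bonferroni undermines; a material gain for it appears only when both ingredients have similar, additive effects.

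**Conclusion.** The point holds as a conditional efficiency gain. No single test loses power under Holm or Shaffer, and both keep 5% familywise error. The gain runs from 0 to about 12 points for one contrast. The upper end requires a contrast with roughly the nominal 80% unadjusted power and both ingredients active with equal, additive effects. If the effects are as large relative to the SD as the planning sentence says, the gain vanishes. Two-sided testing, 28 completers and a common residual variance are assumed throughout. This is an optional improvement, not an error in the plan.

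**What to change.** Before the treatment codes are opened for analysis, replace 'the Bonferroni adjustment' with: *the Holm step-down adjustment (or Shaffer's, if all six pairwise comparisons form the family) of the diet comparisons from the mixed model*. The choice between the two requires stating the family in the same sentence.

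The cost is one phrase and a step-down option in SAS, which the plan already names; no participant, visit or assay is added. The drawback is that simultaneous intervals do not follow directly from a step-down test. Report Bonferroni-width intervals alongside, and note that such an interval may include zero for a contrast the step-down test declares significant.
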